#### Medication relevant for musculoskeletal pain complaints

The recommendation for use of medication was based on the NICE guidelines for treatment of MSK pain complaints, expert consensus groups, and literature review. The recommendation differentiates between phenotype 1–3 and 4–5 (Additional file 2). The rationale for this differentiation is that the duration of pain differs the most between these two groups [28] and that participants with a long-lasting pain may benefit from a different approach than participants experiencing acute pain. All recommendations are graded as “could be considered” or “only if specific indication,” i.e., yellow or red. This is because the use of painkillers in the treatment of MSK pain complaints in general should be limited and very rarely is used as sole treatment, but rather to support other treatment options, e.g., physiotherapy, exercise, and lifestyle changes [32].

#### Referrals to primary or secondary health care, and imaging

Recommendation for referral is adjusted according to participant phenotype and is described in Additional file 2. Treatment recommendations are provided for the use of imaging (X-ray, MR, or other modalities), secondary care referrals (specialist, interdisciplinary pain clinic, or rehabilitation), and other referrals (psychologist, community-based care, or others in primary care). For participants in phenotypes 1 and 2, referral to primary or secondary healthcare and imaging is recommended “only if specific indication.” For phenotype 3, referrals to community-based care or others in primary care “can be considered.” For phenotype 4, referral to secondary care and others “can be considered.” For phenotype 5, referral to secondary care and psychologist is “recommended,” and community-based health-related activities and others in primary care “can be considered.” The rationale for this differentiation is that participants with the best prognosis (i.e., lower phenotypes) should be treated in primary care and by promoting self-management, and the phenotypes with poorer prognosis can consider or are recommended referral as an option if the clinician consider it is useful for the participant.

#### GP`s workflow in the CDSS

The GPs are instructed in how to use the CDSS in their clinical practice and educated in the theoretical basis for the stratified care approach and the implications of the biopsychosocial phenotypes. The participant completes the questionnaires before the appointment with the GP. When the participant has completed the baseline questionnaires, the information is made available for the GP in the CDSS. The GPs are instructed to use the CDSS together with the participant during the consultation and involve the participant in all parts of the CDSS.

The GP starts by opening the patient profile in the CDSS. The GP can then use the patient profile to prepare for the appointment and together with the participant during the consultation. As the patient profile displays several aspects of their subjective history, including biopsychosocial phenotype, pain drawing, expectations, etc., it is recommended that the GP shows the patient profile to the patient and that they choose what to focus on in the current appointment. The GPs are also instructed to ask the participants if they feel that the patient profile properly represents their complaints.

After taking the patient subjective history and using the patient profile together with the participant, the next part of the consultation is the clinical examination. The GP opens the clinical examination screen and records the participant’s main complaint. They then perform the relevant examinations and register the findings and the primary and secondary ICPC-2 diagnosis in the clinical examination screen.

Finally, in the last part of the consultation, the GP summarizes their findings and decides on a treatment-plan for the participant based on the recommendations related to the participant’s phenotype and the personalized treatment recommendations. The GPs are instructed to use the treatment recommendations screen together with the patients to make shared decisions regarding their treatment plan. After the GP has chosen which treatment options to provide for the participant, they can generate a treatment plan containing the chosen treatment options and relevant links to self-management resources which can be sent as a PDF to the participant or printed to paper. Finally, a text summary of the patient subjective history and biopsychosocial phenotype, findings during clinical examination and chosen treatment options can be exported from the CDSS to the participant medical record at the end of the consultation. This makes it possible for the GP to work in the CDSS. As the CDSS is platform independent, i.e., available from any internet browser, it can be used with any established electronic patient journal system.

#### Control group

The control group will receive current care by the GPs randomized to this arm. Usual primary care for MSK pain complaints is known to be variable; for example, some participants may receive advice, prescriptions for medications, and nothing more, some may be asked to return to the GP for follow-up assessment or treatment, whereas others may be referred to other services, including tests and investigations, or treatment services such as physiotherapy, orthopedics, or pain clinics. Participants will answer the same questionnaires as the intervention group at all data collection time points. The GPs in the control group will have access to the login and patient overview and the clinical examination screen. The control group will not have access to the patient profile or the treatment recommendation screen.

#### Criteria for discontinuing or modifying allocated interventions {11b}

The GPs and study participants can opt out at any time point in the study. In this study, the GPs in the intervention group are exposed to a CDSS for stratified care, we do not expect adverse events from use of the CDSS as it only provides decision support for the GP, and the participant is under the GPs care. Any medical condition or change in condition will be followed up by the GP as a part of the participant’s regular care.

### Strategies to improve adherence to interventions {11c}

#### Educating the general practitioners

All GPs participating in the study will receive educating sessions individually or in small groups. Due to the widespread geographic location of the GPs, the education will be performed digitally through video conference applications. The time planned for education sessions is 60 min. The GPs will be educated in the theoretical basics for the stratification algorithm and expected recovery trajectories for the different phenotypes (only intervention), how to use the CDSS, and how to register and report data. All GPs will also receive a follow-up appointment 3–4 weeks after they start including participants. This to improve compliance with the study enrollment and recruitment of participants and to resolve any issues they might have. The education material differs between control and intervention group, and the material is also video recorded and made available for the GPs for support. We will be in regular contact with the GPs participating in the study to investigate if they experience issues with using the CDSS, if there are issues with recruitment, or if they need additional follow-up.

#### Relevant concomitant care permitted or prohibited during the trial {11d}

This is not applicable for this trial. Current care is the comparator, and the intervention is a computerized decision support system providing personalized treatment recommendations and treatment recommendations based on the participants’ biopsychosocial phenotype. As the intervention is a decision support system, its purpose being decision support, there are no restrictions in the type of treatment the GP can provide to the participants outside the CDSS recommendations.

#### Provisions for post-trial care {30}

Not applicable in this trial. Participants in this trial receive treatment from their GP and are covered by the Norwegian System of Patient Injury Compensation.

### Outcomes {12}

#### Primary outcomes

We will use two primary outcome measures:The patient’s global perceived effect (GPE) at 3 months after start of treatment measured on a 7-point Likert scale. The GPE scale will be dichotomized as “improved” (scores 1–2) or “unchanged/worse” (scores 3–7). GPE is recommended as a core outcome measure in pain studies, as it may cover additional aspects to pain relief and physical function that is important to the individual [33].The proportion with a clinically important improvement at 3 months in function measured by the Patient-Specific Function Scale (PSFS; 0–10). An important improvement will be defined as 30% increase on PSFS. The PSFS will also be dichotomized. Percent changes in PSFS scores will be calculated by taking the actual change in score divided by the possible change, to account for baseline values.

GPE and PSFS will also be assessed at 2, 4, and 8 weeks and included in the analysis models for the primary outcomes and presented as secondary analyses.

#### Secondary outcomes

Secondary outcomes will be change in pain intensity last week measured by the Numeric Rating Scale (0–10), health-related quality of life (EQ-5D), general MSK health (MSK-HQ), number of treatments, use of painkillers, sick-leave grading and duration, referral to secondary care, and use of imaging. We will also collect long-term outcomes at 6. Cost-effectiveness of the CDSS will be evaluated using EQ-5D at 6 months and information on treatment cost from the Norwegian Health Economics Administration. Adequacy of care (high value care) will be assessed by type and amount of treatment offered to participants in the different phenotypes. The hallmark is avoidance of overtreatment and health care spending in the phenotypes with few and uncomplicated symptoms and more comprehensive treatment for those in the phenotypes with complicated and high pain impact. Process evaluation will be carried out with semi-structured focus group interviews of GPs and participants to assess users’ acceptance and barriers and map their experience with using the stratified care intervention.

#### Participant timeline {13}

The study aims to recruit participants between 1 May 2022 and 31 March 2023. The participation timeline is further described in Table 1.

**Table 1 Tab1:** Overview of participation timeline

	Study period							
	Enrolment	Baseline	Follow-up					
Timepoint week		0	2	4	8	12	26	52
Eligibility screen	X							
Informed consent	X							
Allocation	X							
Intervention								
CDSS for stratified care		X						
Assessments								
SMS			X	X	X			
Questionnaires		X				X	X	

Overview of participation timeline. As every GP is a cluster, and already allocated to intervention or control group, all participants are allocated at the time of enrolment

#### Sample size {14}

Sample size calculations based on the *clustersampsi* command in Stata for cluster-randomized, controlled trials show that 280 participants and 20 clusters (GPs) are necessary in each arm to detect a difference of 15% in proportions of participants “improved.” These calculations are based on a power of 80%, alpha level of 0.05, intra-class correlation coefficient (ICC) of 0.05, and an average cluster size of 14 participants per GP. Suggestive values for ICC were obtained from a previous project in primary care, and the same data suggest that the proportion of participants reporting “improved” after usual care physiotherapy was 50–58% in the target groups. To account for a 15–20% drop-out among the participants and 5–10% among the GPs, we will include 22 GPs in each arm and 17 participants in each cluster, giving a total of 748 participants.

Sample size calculations determined that fewer participants would be required to achieve 80% power when assessing the proportion of participants who experience a clinically important improvement in their functional status at each follow-up time point using a mixed logistic regression model, and the above sample size calculation therefore was used to determine the required number and size of clusters.

The two primary outcomes will be analyzed by multilevel modeling to account for clustering of individual data and adjust for covariates. A detailed statistical analysis plan will be published before unblinding of study data.

#### Recruitment {15}

Participating GPs will be recruited nationwide using the Norwegian Primary Care Research Network (PraksisNett, www.uib.no/praksisnett), which is a research infrastructure of close to 500 GPs that facilitates recruitment of primary care patients to clinical studies [34]. Additional GPs will be recruited through direct invitation and promotion at conferences and social media targeted at GPs.

Patients making appointments with their participating general practitioner, either online or through a phone call to the GP practice, will be informed about the study by an electronic message (i.e., SMS/Digital Dialog/Doctors office app/website/communication through Helsenorge). This is the message to the patient: “*Dr. X is collaborating with NTNU on a project to improve care for musculoskeletal pain. You can click on this link to read more about the project and decide if you want to participate*.”

Patients interested in participating will be linked to the study’s onboarding page where they can read information about the study and perform self-assessment for inclusion. If the patient is eligible, he/she is presented with an electronic consent form which contains full information about the study. If the patient consent to participation, personal data is registered (including name, phone number, and e-mail address) and a personal identification code (username) is generated. The participant is then forwarded to the electronic questionnaires and completes the questionnaires before the consultation with the GP. The username and the personal identification variables are stored in a separate secure server at NTNU. In addition, an email notification with the new participant’s name and username will be sent to the GP. The GP must have the username for the participant to identify the participant data in the CDSS.

### Assignment of interventions: allocation

#### Sequence generation {16a}

The cluster-randomization will be performed by the clinical research unit (St. Olavs Hospital and NTNU). GPs will be randomized to intervention (stratified care intervention) or control group (current care) in a 1:1 ratio. The randomization will be performed sequentially depending on the recruitment rate; initially, 22 GPs will be randomized; the remaining 22 GPs will be randomized later. GPs dropping out will be replaced by new GPs from a waiting list. The GPs recruited to the waiting list will be randomized with a ratio depending on the allocation status of the GPs dropping out from the study. The clinical research unit use a randomization procedure provided by Microsoft Excel, which is unknown for the research team in the study.

#### Concealment mechanism {16b}

The randomization is performed by a third party (The Clinical Research Unit in Central Norway) and concealed to the researchers and GPs.

#### Implementation {16c}

The randomization is performed by a third party (The Clinical Research Unit in Central Norway) and concealed to the researchers and GPs. The same party will assign the participants (GP) to their interventions.

### Assignment of interventions: blinding

#### Who will be blinded {17a}

The GPs will be unblinded to their assignment. The participants are blinded to which arm their GP is allocated to when they consent to participate in the study and completes the baseline questionnaire. The participants are not blinded after this, as the participants in the intervention participate in the shared decision-making process in using the CDSS at the first consultation. All data analyses will be performed with the cluster allocation concealed. Two researchers will do the analysis, one blinded who did not participate in the project nor in the data collection. The other one will also be blinded but has been central in administrating the data collection and will only work with data where the group allocation is concealed. The research team will secure the blinding of the analysis in collaboration with the clinical research unit involved in the trial.

#### Procedure for unblinding if needed {17b}

Not applicable as the GPs are unblinded to which arm they were allocated, and the participants are unblinded when in the consultation.

#### Plans for assessment and collection of outcomes {18a}

The data from the CDSS is stored at a secure server at NTNU. This includes all participant and GP reported data from the CDSS. The patient-reported data is collected with LimeSurvey [35]. The baseline and follow-up data in the control group is reported in the encrypted case report forms by the GP and returned to NTNU.

An overview of the questionnaires used can be found in Table 2. The online data collection forms are only available to the participants and can be made available upon request.

**Table 2 Tab2:** Single questions and questionnaires to be answered by the participant at baseline and follow-up at weeks 2–52

Questionnaire	Baseline	2^a^	4^a^	8^a^	12	26	52
Demographic variables/background	X						
EQ-5D (health/life quality)	X				X	X	
Sleep and vitality item from 15D	X				X	X	
Patient specific functional scale	X				X	X	
Pain intensity (NRS)	X	X		X	X	X	
Pain mapping	X				X	X	
Workability	X	X	X	X	X	X	
Sick leave	X				X	X	
Anxiety for pain in physical activity (1 question from Tampa Scale)	X	X	X	X			
Örebro Screening Form	X						
Medication	X				X	X	
Expectation (2 questions)	X						
Received treatment last 12 months and effect of treatment	X						
Global perceived effect (1 question)		X	X	X	X	X	
Patient-therapist relationship					X	X	
Benefits and expectations to GP fulfilled?					X	X	
Adherence to treatment plan					X	X	
Most imp. reason for success/non-success					X		
Still receiving treatment from the GP?						X	
Other current diseases or ailments	X						
Red flags	X						
Description of childhood	X						
Health literacy 2 questions	X						
Physical activity HUNT	X				X	X	
HSCL-10 (emotional distress)	X				X	X	
Pain self-efficacy, 2 questions	X	X		X	X	X	
The Keele STarT MSK Tool	X						
Musculoskeletal Health Questionnaire (MSK-HQ)	X				X	X	

^a^Collected by SMS

#### Plans to promote participant retention and complete follow-up {18b}

A 24-h participant hotline is established, so the GPs (and participants) easily can contact the research group with any questions regarding the intervention or system at any time. Also, a support e-mail is established with the same purpose. We will provide a weekly newsletter for the GPs with advice for recruitment and their current recruitment status compared to the status of the other GPs in the study. We will also have weekly/bi-weekly contact with GPs through SMS and social media. Finally, we will arrange a weekly contest where the GP recruiting the most participants the previous week will receive a small prize.

To promote participant retention and completion of follow-up data, the participants’ contributions will be monitored, and participants lacking registration of 3-month follow-up data will be contacted by phone/SMS.

### Data management {19}

#### Data collection and management

Data will be obtained from the participants at baseline before the first consultation, at 3 months and 6 months follow-up. In addition, we will send some questions in weeks 2, 4, and 8 after baseline by SMS or mail. The data will be collected as follows:All participant reported information at baseline and the follow-up time points will be collected using electronic questionnaires, including the SMS questions, through the survey tool LimeSurvey [14]. The participants receive a personal link to the questionnaire via mail, where they can complete the questionnaire online. A complete list of collected data is found in Table 2.The GP will register information from the clinical examination and the treatment plan via the CDSS, where the stratified care intervention is completed.The GP will register treatment provided at baseline and 3 months in an encrypted case report (Additional file 3).

#### Participant and clinician reported information

Table 2 describes all questionnaires and questions reported by the participant and covers demographics and different aspects related to biological, psychological, and social factors associated with pain conditions. User groups consisting of physiotherapists and GPs have been involved in the current project to decide on the questionnaires included below. The time for filling out the questionnaires at baseline is approximately 15 min. We will send a link via SMS with the questionnaires between baseline and 3 months. The GP reports the main problem, ICPC-2 diagnosis, findings from the clinical information, and provided treatment.

#### Registration of treatment prescribed by the GP

The treatment plan decided at the first consultation will be registered by the GP in the CDSS and linked to the participant in the secure server at NTNU. The treatment that was provided between first consultation and 3 months will be reported by the GPs in an encrypted spreadsheet, a “case report form” (Additional file 3).

#### Confidentiality {27}

We will use the same solution for data storage on a secure server at NTNU that was used in the SelfBack project [36] and a RCT study in physiotherapy (REC nr 49,308). The principal investigator can access the server through a username and a personal password, while the GPs can read and retrieve data from their own participants from the secure server via the CDSS. The GP have their personal username and password for the CDSS which is only linked to the GP’s own participants. The key document linking the personal data and username is stored and encrypted on a secure server separate from where the participant data is stored. Access to the key document is restricted by an encryption key, which is kept by the principal investigator. The principal investigator can grant access to the key document by providing the encryption key to other persons in the research project who is working with the data collection. The secure server is backed-up on a daily basis, and back-ups are kept for a 1-year period.

#### Plans for collection, laboratory evaluation, and storage of biological specimens for genetic or molecular analysis in this trial/future use {33}

Not applicable for this study as no biological specimens are collected.

### Statistical methods

#### Statistical methods for primary and secondary outcomes {20a}

We will publish a detailed statistical analysis plan in the ISRCTN registry. The statistical reporting will adhere to the CONSORT statement, including the extension to cluster randomized trials [37, 38]. We will describe GP characteristics as follows sex, age, location (rural/urban areas), years of working in general practice, specialist status, and number of patients under their care. We will also describe participant demographics, including sex, age, and education level to avoid selection bias.

The primary analyses for the primary and secondary outcomes will be intention to treat.

#### Analysis of the primary outcome

The effect of CDSS at 3 months will be estimated for both primary outcomes using three-level mixed logistic regression models. Each primary outcome will be assessed in a separate model that includes the repeated measures of the outcome at 2 weeks, 4 weeks, 8 weeks, and 3 months follow-up as the dependent variable and such that they are clustered by follow-up timepoint (level 1), participants as level 2, and GPs as level 3. Treatment allocation, time point, and an interaction between treatment allocation and time point will be included as independent variables. We will adjust for the stratification variable and possible prognostic variables (age, sex, education, and pain-duration). In addition, when analyzing PSFS, we will adjust for the baseline value.

The treatment effect will be estimated for each time point from the mixed logistic regression models and presented as an OR with 95% confidence intervals.

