The Keele STarT MSK tool mainly focused on function and disability, pain and coping, comorbidity, and the impact of pain, with little emphasis on psychological and social factors, sleep, and work ability. In addition, there were issues with poor fidelity to the system among the GPs. We therefore developed a novel method to stratify patients with MSK pain complaints using latent class analysis, to include a broader biopsychosocial approach [27]. Based on 11 generic prognostic factors, we identified five phenotypes of patients irrespective of their pain presentation (neck, shoulder, back, knee, hip, and multisite pain) [28]. The five phenotypes clearly distinguished patient subgroups by type and level of symptoms, both in a developmental sample and a validation sample [28]. Furthermore, the phenotypes had different trajectories for recovery and symptoms over 1 year follow-up, indicating that the prognostic phenotyping provided a clinically meaningful subgrouping of patients with MSK pain complaints [10]. The phenotype model includes a more comprehensive coverage of prognostic factors across the biopsychosocial domain and discriminatory ability in separate samples and over time. As such, the phenotype model may prove superior to the STarT MSK tool in stratifying patients into more distinguished subgroups and, thus, improve treatment matching and treatment outcome. However, the degree of heterogeneity in patients with MSK pain complaints requires a high predictive performance of the stratification tool. To compensate for this heterogeneity, the addition of personalized treatment recommendations may further enhance the benefits of a stratified care.

To improve GPs fidelity and further refine the stratified care approach, we incorporated the phenotyping of the patients and the matched treatment options in a computerized clinical decision support system (CDSS) for GPs. In addition, we added personalized treatment recommendations based on patient-specific factors to the CDSS. In this study protocol, we describe the randomized controlled trial for evaluating the effectiveness of CDSS for stratified care for patients with common MSK pain complaints in general practice—the SupportPrim project.

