### Who will take informed consent? {26a}

The GPs identify patients with MSK pain complaints making appointments to see their GP. The patients identified by the GP then receive a link to online information about the study with invitation to participate in the study. If patients are willing to participate, they perform self-eligibility testing and are only allowed to participate if they meet the inclusion criteria. Patients eligible for the study sign the informed consent online and automatically receives an email granting them access to the baseline questionnaires. This is a cluster-randomized controlled trial (RCT), and participants will therefore not be informed about random allocation of their GP to intervention arms. They will be asked for consent for data collection related to the study. The GPs are not involved in obtaining informed consent, the questionnaires, and consent form are available to the participants online. Finally, the GPs will check the patient’s eligibility at the first consultation, including verification that the patient’s main problem is MSK pain complaint and comprehends the Norwegian language.

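### The primary GPE model leaves out baseline severity and phenotype, although unblinded GPs identify and check patients after allocation

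*Protocol article*

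**What the plan says.** **Recruitment and knowledge of allocation.** The note to the participation timeline (Table 1) says each GP is already allocated when a patient enrols. Under the blinding section, "The GPs will be unblinded to their assignment". The consent section says "The GPs identify patients with MSK pain complaints making appointments to see their GP". After the patient's own online eligibility test and consent, it adds "Finally, the GPs will check the patient’s eligibility at the first consultation". The two checks it names are that the main problem is a musculoskeletal pain complaint and that the patient understands Norwegian.

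**What each arm's GP can see.** The login section makes the patient's answers available to the GP as soon as the baseline questionnaire is complete. Intervention GPs may use the profile screen, with the phenotype, to prepare for the visit. The control group section withholds that screen from control GPs. Only intervention GPs are taught the expected recovery course by phenotype.

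**The models.** The section on the primary outcome names the covariates for both models: the stratification variable, age, sex, education and pain duration. It then adds, for function only, "In addition, when analyzing PSFS, we will adjust for the baseline value". Phenotype appears later only as an exploratory subgroup. The background section says that "the phenotypes had different trajectories for recovery and symptoms over 1 year follow-up".

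**Selection bias.** The statistical methods section says "We will also describe participant demographics, including sex, age, and education level to avoid selection bias".

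**The concern.** In a cluster trial where patients enter after allocation, randomising GPs does not by itself balance the patients. A GP who knows the arm can influence, even unintentionally, who is put forward and who is judged eligible. If the arms then differ in severity or prognosis, that difference goes into the treatment effect unless the model accounts for it.

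Describing sex, age and education shows an imbalance in those three variables. It does not correct one, and none of the three measures severity. For function, the baseline score covers part of the gap. GPE is a rating of change and has no baseline value, so a severity term has to come from another variable. The plan collects several at baseline and uses none of them.

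Two things are at stake: residual bias in one of the two primary results, and some precision given up although the data are in hand.

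**Working it through.** **1. The plan's own sample size.** The inputs are "power of 80%, alpha level of 0.05, intra-class correlation coefficient (ICC) of 0.05, and an average cluster size of 14 participants per GP" and "280 participants and 20 clusters (GPs) are necessary in each arm to detect a difference of 15% in proportions". I assume a two-sided test and a control proportion of 50%, the low end of the stated 50–58%, so 50% against 65% with mean 57.5%.

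n per arm before clustering = [1.96 × √(2 × 0.575 × 0.425) + 0.842 × √(0.50 × 0.50 + 0.65 × 0.35)]² / 0.15² = 169.3, rounded up to 170.

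Design effect = 1 + (14 − 1) × 0.05 = 1.65. Then 170 × 1.65 = 280.5, against 280 stated; power at 280 per arm is 80.1%. The figure reproduces and is not in question.

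**2. Are the omitted covariates available and untouched by treatment?** Yes. Table 2 lists the function scale, pain intensity, emotional distress (HSCL-10) and the MSK-HQ at baseline. Both arms answer the same questionnaires, before the first consultation and while patients are blinded to the arm. The planned subgroup analysis by phenotype needs the phenotype in both arms anyway.

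**3. Possible bias (assumed inputs).** The documents give no association between severity and GPE and no expected imbalance. Suppose there is no true effect, 50% improve, severity is standard normal with log odds ratio −b per SD, and one arm is d SD less severe. The proportion improved in that arm is the average of 1 / (1 + exp(b(x − d))) over a standard normal x. Type I error uses 280 / 1.65 = 169.7 effective patients per arm, so SE = √(2 × 0.25 / 169.7) = 0.054.

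| Odds ratio per SD (b) | Imbalance d | Spurious difference, points | Two-sided type I error |
|---|---|---|---|
| 0.74 (0.3) | 0.1 | 0.7 | 5.2% |
| 0.74 (0.3) | 0.3 | 2.2 | 6.9% |
| 0.61 (0.5) | 0.2 | 2.4 | 7.2% |
| 0.50 (0.7) | 0.1 | 1.6 | 6.0% |
| 0.50 (0.7) | 0.3 | 4.7 | 14% |

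These figures are before any adjustment. If pain duration correlates with severity at r, adjusting for it removes about r² of the bias: 9% at r = 0.3 and 25% at r = 0.5. The largest value then falls from 4.7 to about 4.3 or 3.5 points. The direction could favour either arm.

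**4. Possible gain in precision (assumed inputs).** Shrinking the outcome variance by (1 − R²), with the ICC unchanged, makes the effective size 169.7 / (1 − R²):

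| Extra R² | Power |
|---|---|
| 0% | 80.1% |
| 2% | 80.9% |
| 5% | 82.1% |
| 10% | 84.1% |

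The three odds ratios in step 3 correspond to an R² of about 2%, 6% and 10% when nothing is already explained by other covariates. The increment over the planned covariates would be smaller.

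**The case against.** The best defence is that the plan already limits the problem. Patients test their own eligibility, consent online without the GP, and do not know the arm at consent or at baseline. The model adjusts for four prognostic variables. The medication section says pain duration is what differs most between phenotypes 1–3 and 4–5, so part of the phenotype's information is already in the model. All of this stands and rules out saying that selection bias is uncorrected or that precision is simply unused. It does not govern whom the GP identifies, and pain duration is at best a partial stand-in for severity. The stratification variable does not fill the gap either: GPs are the randomised unit, and the sequence generation section names no such variable.

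A second objection is that the power figures are on the risk-difference scale while the plan estimates an odds ratio from a mixed logistic model. There, a prognostic covariate does not shrink the standard error of the log odds ratio, and the conditional odds ratio itself changes. That also stands, so the gain is only a rough guide.

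Three stronger readings are tempting, but the documents do not support them:

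- A reader might infer that the consent and recruitment sections contradict each other, one having the GP identify patients and the other sending a message to those who book. They can be two parts of one process: the GP identifies, and the link goes out electronically. Nothing says the message is automatic.
- A reader might infer that intervention GPs remove patients from the analysis because of phenotype. The named checks concern neither severity nor phenotype. No section says that patients who fail them are dropped, and the primary analysis is stated as intention to treat.
- A reader might want the invitation procedure changed. Recruitment was planned to end on 31 March 2023 and this version is dated 27 February 2023, so little could be gained.

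**Conclusion.** The point holds as a worthwhile and nearly free improvement to the GPE analysis. It is not evidence that the trial is biased. The covariates are named as a fixed list, whereas the section on secondary outcomes gives its list as examples, so this is a stated choice and not a detail left open.

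The size is uncertain. Under the assumed imbalances of 0.1 to 0.3 SD and odds ratios of 0.74 to 0.50 per SD, the spurious difference is about 0.7 to 4.7 points against a 15-point target. That is an upper-end range because the planned covariates would absorb some of it. The gain in power is roughly 1 to 4 points for an extra R² of 2 to 10%. The weakness is specific to GPE, since the function model already carries its baseline score.

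**What to change.** Before unblinding:

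1. Prespecify phenotype (five levels) and a baseline severity measure (pain intensity and/or the function score) as covariates in the primary GPE model, alongside those already listed.
2. State that every consented patient with baseline data belongs to the intention-to-treat set, whatever the GP's later eligibility check. The model then uses those with at least one follow-up value, as already planned.
3. Report by arm how many patients the GP judged ineligible.

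The first two need wording only, and no new patient questionnaire data are required. There are three costs. Some patients whom the GP judged ineligible, presumably few, stay in the analysis. The odds ratio becomes conditional on more covariates, so its meaning shifts slightly. Only measured selection factors are addressed; selection on anything unmeasured remains, which is why the counts by arm should be reported as well.
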